#### Secondary outcome measures

A single booklet of outcome questionnaires will be provided to all trial participants at baseline and 6 and 9 months post-treatment. These are as follows:EORTC QLQ-C30This is a validated measure to assess the quality of life of cancer patients [41]. It comprises a 30-item questionnaire incorporating five functional scales (physical, role, cognitive, emotional and social), three symptom scales (fatigue, pain and nausea and vomiting), a global health status/quality of life scale and a number of single items assessing additional symptoms commonly reported by cancer patients and perceived financial impact of the disease.EQ-5D-3LThis is a validated generic, health-related, preference-based measure comprising five domains: mobility, self-care, usual activities, pain and discomfort and anxiety and depression. Each domain has three levels (no problems, some problems and a lot of problems). The EQ-5D-3L scoring system defines 243 possible health states. The questions are complemented by a visual analogue scale (VAS), on which respondents are asked to indicate their current health [42].ICECAP-A (ICEpop CAPability measure for Adults)This is a measure of capability for the general adult population [43]. The ICECAP-A covers five attributes of wellbeing: attachment, stability, achievement, enjoyment and autonomy.Client Service Receipt Inventory (CSRI)This is an adapted version of a standardised measure using self-report service user data to evaluate and cost service use, including all GP visits and unscheduled secondary care in both arms of the study [44, 45].

Additional data to be captured will include the following:e)Patient demographics, cancer type and stage, type of treatment received and co-morbidity at baseline (from medical records and patient confirmation).f)Data on the pattern, timing and method of detection of relapse and on survival (recorded using a Serious Adverse Events form).

We anticipate that on average patients would complete all questionnaires in about 20 min on each occasion.

The number of patients offered the study will be logged to identify the proportion of patients that decline to take part. Patients who decline to consent will be asked if they would be willing to provide any reason(s) why they preferred not to take part.

Data will aim to be collected from all willing participants, even in the case of a withdrawal or non-compliance with the intervention.

### Data collection/storage

Data collection, cleaning and analysis will be undertaken by NWORTH using standard, secure, anonymous procedures for handling patient data. The fully auditable MACRO data management system will be used to ensure best practice. The health economics and patients’ demographic data will be transferred from NWORTH to CHEME (Centre for Health Economics and Medicines Evaluation) for further analysis.

### Statistical methods

Descriptive statistics will be reported, including clinical and demographic characteristics of those recruited. To assess the feasibility of a full RCT, the recruitment and retention rates will be calculated. A future full RCT will be considered feasible if the recruitment rate is at least 50% and retention rate is no less than 50%. Additionally, the patient eligibility rate and questionnaire completion rates will be calculated to provide further evidence for the appropriateness of a full trial and associated measures.

Exploratory analysis will also be conducted around the assessments of QoL with the purpose of estimating key parameters for powering the main RCT but not to provide definitive results for the study. Effect sizes of the differences in final scores calculated from the EORTC QLQ-C30 will be calculated between the groups as randomised for the study endpoint. The effect size will be used to inform future sample size calculations for a larger, multi-centre RCT.

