### Design

The current study will be a parallel-group randomised controlled feasibility trial design comparing nurse-led intervention (treatment group) with standard care (control group) to assess recruitment and retention rates and acceptability of randomisation and to inform the sample size calculation for a future trial.

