### Sample size

We estimate 30% will not fit the inclusion criteria whilst an unknown proportion of the remainder will not enter the study, either through not wishing to consent or for other reasons. The extent of patient acceptability is unknown but for planning purposes, we will assume 50% acceptance. Assuming a throughput of approximately 150 newly diagnosed cases, we hope to randomise 50 participants from the recruiting centres into the study during a period of 6 months. It is thought this would be sufficient to inform a sample size of a future full trial [35] and enable a reasonably diverse group to fully assess the acceptability of the trial.

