### Randomisation

Following their 3-month appointment, consenting patients will complete the baseline measures (see below) then be randomised at the end of the 3-month review appointment. Patients will be randomised on a 1:1 ratio by the North Wales Organisation for Randomised Trials in Health (NWORTH) using a dynamic, independent, secure, web-based, randomisation procedure that can be accessed 24 h a day [36]. Patients will be randomised to one of the two arms of the study: standard care or nurse-led intervention. Site and disease type will be included as stratification variables. The participants, research nurse, CNSs and trial management will be unblinded during this trial. All other members of the team, especially the trial statistician, will remain blinded.

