### Measures

#### Primary outcome measures

The primary outcome measures of the feasibility trial will be:Patient recruitment rateThis will be calculated from the total number of eligible patients invited to take part in the study and the number of patients giving written consent to participate in the study.Patient attrition rateThis will be calculated from the number of patients who gave written consent and the number of patients who have completed any measures, regardless of their completion rate.

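### The feasibility rule uses one overall retention rate that can count baseline-only patients as retained, so it is insensitive to loss of an arm after allocation

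*Protocol article*

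**What the plan says.** The article's Design section says that the trial is meant "to assess recruitment and retention rates and acceptability of randomisation", and the Aim section adds acceptability of the new intervention. The Statistical methods section turns this into a decision rule: "A future full RCT will be considered feasible if the recruitment rate is at least 50% and retention rate is no less than 50"%. No section sets a threshold for a single arm or a limit on the difference between arms.

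The Primary outcome measures section bases attrition on "the number of patients who gave written consent and the number of patients who have completed any measures, regardless of their completion rate". The Randomisation section gives the order of events: "consenting patients will complete the baseline measures (see below) then be randomised at the end of the 3-month review appointment". It also says "The participants, research nurse, CNSs and trial management will be unblinded during this trial".

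The Nurse-led intervention section names the 9-month data collection as the study endpoint, but neither the attrition definition nor the feasibility rule refers to it.

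**The concern.** Two features of the rule combine.

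- **One overall rate.** The denominator is everyone who consented, and consent comes before randomisation, so the rate belongs to the whole trial. It cannot tell balanced loss from loss concentrated in one arm.
- **No time point.** A patient who completes the baseline booklet has completed a measure. If she is lost straight after allocation, the definition still counts her as retained.

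Unequal loss is plausible here. Participants know their allocation, and only the intervention arm gives up its usual hospital reviews. Follow-up questionnaires are completed at clinic appointments in standard care, with post as the fallback, but by post in the intervention arm. That difference alone could produce different return rates.

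What is at stake is the decision to go on to a full trial. Heavy loss from one arm after allocation would make a full randomised comparison hard to interpret, and the published rule could still answer that the trial is feasible.

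**Working it through.** **Inputs from the article**
- Sample size: "we hope to randomise 50 participants from the recruiting centres into the study during a period of 6 months".
- Throughput: "Assuming a throughput of approximately 150 newly diagnosed cases", with 30% assumed ineligible and 50% assumed to accept.
- Allocation: "Patients will be randomised on a 1:1 ratio".
- Rule: retention of at least 50%. Retention is taken as the complement of the attrition rate under Primary outcome measures, since no other definition is given.

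**The plan's own figure.** 150 × (1 − 0.30) × 0.50 = 52.5, which agrees with a rounded target of 50. At 1:1 that is 25 per arm.

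**Step 1: the definition read literally.** Suppose 50 patients consent, complete baseline and are randomised, and none returns a follow-up booklet. All 50 have completed a measure, so retention is 50/50 = 100% and the criterion is met with no follow-up data in either arm.

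**Step 2: retention read as return of follow-up data.** This is an assumption, because the article does not say it. The rule then needs 25 of 50:
- (19 + 6)/50 = 50%: passes with arms at 76% and 24%.
- (20 + 5)/50 = 50%: passes with arms at 80% and 20%.
- (25 + 0)/50 = 50%: passes with arms at 100% and 0%.

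**Step 3: how often this would happen.** Let X and Y be the numbers retained in the two arms, independent binomials with n = 25. The overall rule passes if X + Y ≥ 25. A per-arm 50% rule passes if X ≥ 13 and Y ≥ 13, because 12/25 = 48% falls short. The article gives no arm-level retention, so the true rates below are assumptions shown over a range.

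| True retention, arm 1 / arm 2 | P(overall rule passes) | P(per-arm rule passes) |
|---|---|---|
| 95% / 5% | 0.64 | <0.001 |
| 95% / 20% | 0.97 | <0.001 |
| 90% / 20% | 0.89 | <0.001 |
| 90% / 30% | 0.98 | 0.02 |
| 80% / 30% | 0.84 | 0.02 |
| 80% / 20% | 0.57 | <0.001 |

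**Step 4: cost of a per-arm rule when the arms are equal.** The overall rule passes with P(Bin(50, p) ≥ 25), and the per-arm rule with P(Bin(25, p) ≥ 13)².

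| True retention in both arms | Overall rule | Per-arm rule |
|---|---|---|
| 55% | 0.80 | 0.48 |
| 60% | 0.94 | 0.72 |
| 70% | 0.999 | 0.97 |
| 80% | >0.999 | 0.999 |

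The exact 95% confidence interval for 13/25 is 31% to 72%.

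**The case against.** A reader might infer that acceptability of randomisation is not tested at all. The article does not support that. Patients are told before consenting that they will be randomly assigned, the recruitment rate has its own 50% criterion, and decliners are logged and asked for reasons. That evidence stands, but all of it concerns acceptability before allocation.

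Dislike of an allocation also need not show as missing data. The article intends to collect data from willing participants even after withdrawal or non-compliance, so retention means data return and not adherence to the allocated care. This stands too: retention by arm is only an indirect signal of rejection.

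Imbalance may also be visible elsewhere. The CONSORT diagram is to show loss, the Health economics section describes EQ-5D-3L and ICECAP-A completeness in both arms, and questionnaire completion rates are offered as further evidence. The figure and any analysis plan are not shown, so by-arm reporting cannot be presumed absent. Reporting would not alter the stated rule, however, because none of these items enters it.

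The splits worked above are large, and nothing in the article says they are likely. One overall criterion is a defensible starting point for a 50-patient feasibility study, and a hard cut-off on 25 patients is weak evidence. These points limit how firmly a per-arm rule should be read, but they do not make the present rule sensitive to the loss of an arm.

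**Conclusion.** The point holds as a weakness in the decision rule. The rule can be met with one arm largely lost after unblinded allocation and, on the literal definition, with follow-up data missing in both arms. The definition is the root problem: adding a by-arm condition while baseline completion still counts as retention would change almost nothing.

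The probabilities rest on 50 randomised at 1:1, retention read as return of follow-up data, independent binomial loss, and assumed arm rates. On those terms, an arm retaining 30% usually passes unnoticed (0.84 to 0.98 when the other arm keeps 80% to 90%). So does an arm retaining 20% if the other keeps 90% or more (0.89 to 0.97). Near-total loss of one arm is less sure to pass (0.64 at 95%/5%). That the rate is overall is an inference from the single threshold and the consent-based denominator; the article does not use the word pooled.

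**What to change.** Amend the attrition definition and the feasibility sentence together:

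1. Define retention as the proportion of randomised patients who provide outcome data at 9 months, the study endpoint the article already names.
2. Require retention of at least 50% in each randomised arm.
3. Report the between-arm difference in retention with its confidence interval.

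The 9-month questionnaires are already planned in both arms, so no new data are needed. The cost is a noisier and stricter criterion at about 25 per arm. It is material when true retention is close to the threshold (the equal-arm figures at 55% and 60% in the working) and small from about 70% upward. Given the wide interval around a result such as 13/25, the arm-level results should be read alongside the estimated difference.

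### The exploratory QLQ-C30 effect size is defined on final scores with no stated use of the pre-randomisation baseline: valid, but less precise than it need be, and incomplete for planning a baseline-adjusted full trial

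*Protocol article*

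**What the plan says.** The Statistical methods section of the protocol article specifies the quality-of-life analysis in one sentence: "Effect sizes of the differences in final scores calculated from the EORTC QLQ-C30 will be calculated between the groups as randomised". The time point is the study endpoint, which the Nurse-led intervention section sets at 9 months after treatment. The next sentence passes the effect size to the sample size of a larger trial. The section calls the analysis exploratory and says that its purpose is to estimate parameters for powering that trial.

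The information for an adjusted analysis is already collected. Under Secondary outcome measures, the questionnaire booklet "will be provided to all trial participants at baseline and 6 and 9 months post-treatment", and the Randomisation section places the baseline measures before allocation. On allocation it adds: "Site and disease type will be included as stratification variables". The analysis sentence mentions neither the baseline score nor these factors.

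The Aim section sets two goals that bear on this: to learn SDs and effect sizes for the power calculation, and to pilot the analysis that the full trial would use.

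**The concern.** A trial that measures the same questionnaire before randomisation and at the endpoint would ordinarily adjust the endpoint comparison for the baseline score. This removes the part of the outcome variance that baseline explains. It matters here because the purpose of the analysis is parameter estimation in a small sample.

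Two things are at stake. The first is precision: the effect estimate carries noise that could be removed with data in hand. The second is completeness: a full trial analysed by ANCOVA is planned from the residual SD, or equivalently from the final-score SD and the baseline to follow-up correlation. The stated analysis gives the final-score SD but not the correlation, so it does not fully pilot a baseline-adjusted analysis.

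**Working it through.** **The plan's own figure.** The Sample size section gives three inputs: "Assuming a throughput of approximately 150 newly diagnosed cases", "We estimate 30% will not fit the inclusion criteria" and "for planning purposes, we will assume 50% acceptance". The product is 150 × (1 − 0.30) × 0.50 = 52.5, which agrees with the rounded target: "we hope to randomise 50 participants from the recruiting centres into the study during a period of 6 months". With 1:1 allocation (Randomisation section), this is 25 per arm. The article gives no alpha, power, SD or QLQ-C30 effect size, so there is no power-based figure to reproduce.

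**Assumption.** The baseline to 9-month correlation, ρ, is not in the article. I take 0.3, 0.5 and 0.7.

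**Precision at 25 per arm, in SD units.**
- Final scores only: SE = √(2/25) = 0.283. The 95% half-width is 2.01 × 0.283 = 0.57.
- Baseline-adjusted: SE = √(2/25) × √(1 − ρ²).

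| ρ | 1 − ρ² | Variance removed | SE | 95% half-width | Unadjusted ÷ adjusted variance |
|---|---|---|---|---|---|
| 0.3 | 0.91 | 9% | 0.270 | 0.54 | 1.10 |
| 0.5 | 0.75 | 25% | 0.245 | 0.49 | 1.33 |
| 0.7 | 0.51 | 49% | 0.202 | 0.41 | 1.96 |

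The formula ignores the cost of estimating the baseline slope, a variance factor of about 1 + 1/(2n − 4). At n = 25 this is 1 + 1/46 = 1.02, so the gain at ρ = 0.3 is nearer 7% (0.91 × 1.02 = 0.93).

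**At the retention threshold.** Statistical methods accepts retention down to 50%, which leaves 12.5 per arm, taken as 13. The half-width is then 0.81 SD unadjusted, and 0.77, 0.70 and 0.58 adjusted for ρ = 0.3, 0.5 and 0.7.

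**What the correlation is worth to the full trial.** This illustration assumes a true effect of 0.3 final-score SD, two-sided 5% and 90% power. The number per arm is 2 × (1.96 + 1.2816)² × (1 − ρ²)/0.3², rounded up.
- ρ not used: 234 per arm, 468 in total.
- ρ = 0.3: 213 per arm, 426 in total.
- ρ = 0.5: 176 per arm, 352 in total.
- ρ = 0.7: 120 per arm, 240 in total.

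**How well this study could estimate ρ.** By Fisher's z, with an observed ρ of 0.5 in 50 patients: atanh(0.5) ± 1.96/√47 = 0.549 ± 0.286. The 95% CI for ρ is about 0.26 to 0.68. The multiplier 1 − ρ² could then lie anywhere from 1 − 0.26² = 0.93 to 1 − 0.68² = 0.54. If a full trial were planned on 0.5 and the truth were 0.26, it would have 0.75/0.93 = 0.81 of the patients needed.

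**Stratification factors.** There are three hospitals and at least four disease types, so at least 12 cells for 50 patients, or about 4 per cell. Arm, baseline, site and disease type need 1 + 1 + 2 + 3 = 7 terms plus an intercept. The gain from site and disease type cannot be computed from the article.

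**The case against.** The strongest objection is that the article names an outcome, a time point and the analysis groups, and nowhere says that covariates are excluded. ANCOVA also estimates a difference in final scores, and the choice of covariates is commonly left to a statistical analysis plan, which is not shown here. This stands in part. A reader might infer that the sponsor has decided against adjustment; the text does not support that. It does fix the quantity and its use in the next trial's sample size, and it gives the baseline no role, so the wording deserves completing.

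A reader might also infer that the plan uses the wrong analysis and the wrong SD. It does not. With complete follow-up, the final-score comparison is unbiased under randomisation. The final-score SD is a legitimate planning input, since the ANCOVA sample size is the final-score sample size times (1 − ρ²), and used alone it errs towards a larger trial. Nor does it follow that the full trial will be 1.33 to 1.96 times too large. That range needs ρ between 0.5 and 0.7 and planners who ignore the correlation, although the collected scores would let them calculate it at any time.

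Chance baseline imbalance is not a further harm. At ρ = 0.6, a one-SD imbalance of 0.283 moves the unadjusted effect by 0.6 × 0.283 = 0.17 SD. But 0.17² ≈ 0.029 is 36% of 0.283² = 0.080, and 36% is ρ², the variance already counted above.

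Finally, adjustment does not rescue the estimate: at 25 per arm the half-width stays between 0.41 and 0.54 SD. That is correct, and it limits the weight of the point.

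**Conclusion.** The point holds as a minor one about precision and completeness. As stated, the quality-of-life effect size makes no use of a baseline score that the trial collects before randomisation. For an assumed ρ of 0.3 to 0.7, 9% to 49% of its variance could be removed; put the other way, the unadjusted variance is 1.10 to 1.96 times the adjusted one. The size rests entirely on that assumed range. The stated analysis also does not supply the residual SD or the correlation for a baseline-adjusted full trial.

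The analysis is not invalid and its SD is not wrong. Severity is minor: the primary outcomes are recruitment and attrition, the feasibility criteria use only recruitment and retention rates, and the quality-of-life comparison is declared exploratory.

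**What to change.** State, in the protocol or the statistical analysis plan, that the 9-month QLQ-C30 difference will be estimated by ANCOVA on arm and baseline score. Add site and disease type, with sparse disease categories merged, only where the numbers analysed allow it.

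Report:
- the adjusted difference with its 95% CI;
- the final-score SD and the residual SD;
- the baseline to 9-month correlation with its 95% CI.

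In the full-trial sample size, use a cautious value from the lower part of the correlation's interval rather than the point estimate, because about 50 patients will estimate it poorly.

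The cost is wording and a few degrees of freedom: one for the baseline score, and up to five more for three sites and four disease types. No new data are needed.

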## Methods/design

### Aim

The primary aim of the current study is to evaluate the feasibility of conducting a randomised trial comparing nurse-led telephone follow-up with standard, hospital-based, medical follow-up. Feasibility will be determined by the ability to recruit and retain patients to the study the ability to collect regular data and to evaluate the acceptability of implementing this new intervention.

The secondary aim of this feasibility study is to gain knowledge of standard deviations and effect sizes on the study outcome measures to inform the power calculation for a future full trial.

The final aim is to pilot the statistical and health economics analysis that would be required within a future full trial that will ultimately determine the effectiveness and cost-effectiveness of the new nurse-led telephone follow-up approach.

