In addition to the nurse-led intervention, patients will be asked to complete the same set of outcome questionnaires as patients in the standard care arm. The outcome questionnaires will be completed at baseline (prior to randomisation) with assistance from the research nurse or CNS at the 3-month follow-up appointment. Patients will receive the same set of outcome questionnaires by post at 6 months post-treatment and within a week of their 9-month telephone follow-up and will be asked to return them in a self-addressed, pre-stamped envelope.

For this study, we will consider the study endpoint to be the 9 months post-treatment data collection. After the 9-month data collection point, the intervention and control arm patients will continue with follow-up care as the clinician advises and is available to the local service.

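### The QLQ-C30 effect size that will size the full RCT is fixed on 9-month final scores, with no stated role for the 6-month scores collected from everyone

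*Protocol article*

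**What the plan says.** Statistical methods names one between-group QoL calculation for planning the full trial: "Effect sizes of the differences in final scores calculated from the EORTC QLQ-C30 will be calculated between the groups as randomised". That contrast is taken at the study endpoint, and the Nurse-led intervention section fixes the time point: "we will consider the study endpoint to be the 9 months post-treatment data collection". Statistical methods then states the use: "The effect size will be used to inform future sample size calculations for a larger, multi-centre RCT".

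Under Secondary outcome measures, the QLQ-C30 is part of a booklet given three times: "A single booklet of outcome questionnaires will be provided to all trial participants at baseline and 6 and 9 months post-treatment". No sentence brings the 6-month score into the effect size.

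Two other statements are broader. The Aim section wants to "gain knowledge of standard deviations and effect sizes on the study outcome measures to inform the power calculation for a future full trial", without tying the SD to a visit. Statistical methods introduces the QoL work generally: "Exploratory analysis will also be conducted around the assessments of QoL with the purpose of estimating key parameters for powering the main RCT". Questionnaire completion rates are also planned, not limited to one visit.

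**The concern.** The article names a contrast, a time point and a use, so this is a stated analysis choice and not merely silence about missing data. Read plainly, it is a comparison of 9-month scores between arms. Three features of this trial make that a weak basis for planning.

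- **Tolerated loss.** Statistical methods would call a full RCT feasible with retention as low as 50%. Under Primary outcome measures, attrition is counted against completion of any measure, so a woman can count as retained without a 9-month score.
- **Different collection by arm.** Standard-care participants complete questionnaires at the end of their clinic appointments, with post as fallback (Standard care). Intervention participants receive them by post at both later visits (Nurse-led intervention). The reasons for non-return could therefore differ between arms, which is the setting in which a comparison of observed final scores is biased.
- **Carry-over.** The article says that the study pilots the statistical analysis for the full trial, so a contrast fixed here may be reused.

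At stake is the effect size behind the next trial's sample size.

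**Working it through.** **1. The plan's own figure.** From Sample size: 150 cases, 30% ineligible, 50% acceptance. 150 × (1 − 0.30) × 0.50 = 52.5, consistent with the approximate target of 50, or 25 per arm at 1:1. The article gives no alpha, power, effect size or SD, so there is no power calculation to reproduce.

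**2. Size of the possible bias.** Assumptions, none from the documents: no true difference; 6-to-9-month correlation ρ = 0.7; 50% retained in each arm; in one arm the log-odds of being retained rise by 1 per SD of the 6-month score; loss in the other arm is random.

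Bias of the observed 9-month difference = ρ × mean standardised 6-month score among those retained = 0.7 × 0.413 = 0.289 SD. Simulation with 25 per arm gives 0.288. Regression on the 6-month score brings it to 0.00, and the empirical standard deviation of the estimated difference falls from 0.40 to 0.36.

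**3. Other loss patterns.** Large-sample simulation, 200,000 per arm; assumed true d = 0.30, SD = 1, correlation 0.6 among all three visits, the same logistic slope, and equal retention in the two arms. Cells show d from observed 9-month scores, with n per arm at two-sided alpha 0.05 and 90% power in brackets. The true d needs 234 per arm.

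| Retained | Random loss | Same selective loss in both arms | Selective in standard care only | Selective in intervention only |
|---|---|---|---|---|
| 90% | 0.295 (242) | 0.307 (224) | 0.240 (365) | 0.359 (164) |
| 80% | 0.300 (234) | 0.309 (221) | 0.202 (517) | 0.409 (126) |
| 70% | 0.294 (243) | 0.308 (222) | 0.150 (934) | 0.462 (99) |
| 50% | 0.299 (236) | 0.313 (215) | 0.053 (7,368) | 0.559 (68) |

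The formula in step 2 agrees with the last row: 0.6 × 0.413 = 0.248, and 0.30 − 0.248 = 0.052, 0.30 + 0.248 = 0.548 (simulated raw differences 0.053 and 0.550). The observed SD lies between 0.969 and 1.000 throughout, so it falls by about 3% at most. Using baseline and 6-month scores returns d between 0.294 and 0.303 in every cell. Because retention was set equal in the two arms, equal retention rates would not reveal the problem.

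**4. Precision gained under random loss.** With a fully observed 6-month score, the large-sample variance ratio for the 9-month mean is 1 − ρ²(1 − f), where f is the fraction retained. With ρ = 0.7:
- f = 0.5: 1 − 0.49 × 0.5 = 0.755, so 25 completers are worth 25/0.755 = 33.1.
- f = 0.8: 1 − 0.49 × 0.2 = 0.902.

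**5. Chance error for comparison.** SE(d) = √(2/n + d²/(4n)), with d = 0.30.
- n = 25 per arm: √(0.0800 + 0.0009) = 0.284, 95% half-width 0.56; SD interval 0.83 to 1.25 times the estimate.
- n = 12 per arm: √(0.1667 + 0.0019) = 0.411, half-width about 0.80; SD interval 0.77 to 1.42 times the estimate.

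**The case against.** A reader might infer that the effect size will come only from women with a 9-month score, that the 6-month QLQ-C30 is never used, and that both the effect size and the SD will be biased. The documents do not support any of these as statements of fact. A 9-month endpoint fixes the target, not the estimator; a repeated-measures model or imputation would fit the same wording. The 6-month score is not excluded from the exploratory QoL work or the completion rates. The SD is not tied to 9 months, and its bias is small in every scenario examined.

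Handling of missing scores is commonly left to the SAP or the full protocol. Neither is shown, so its absence here is not a fault.

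The 0.29 SD figure needs heavy loss, driven by the 6-month score, in one arm only. The 50% is a feasibility floor, not an expected loss. The article also aims to collect data from willing participants after withdrawal, which reduces the problem at source. The return to 0.00 is built into the simulation, because loss was made to depend only on a score that was observed. The analysis is labelled exploratory, and the bias is smaller than the chance error.

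All of this stands and limits the point. It does not remove it: the one contrast named as an input to the future sample size has no stated role for an outcome wave collected from everyone. Bias is not reflected in a confidence interval, and using the 6-month scores also reduces the chance error.

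**Conclusion.** The point holds in a limited form. The article defines the QLQ-C30 effect size on 9-month final scores and states no role in it for the 6-month scores. If observed 9-month scores alone are compared, information is lost, and loss related to health differently in the two arms could move the effect size either way.

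The size is conditional: about 0.3 SD at 50% retention with one-arm selective loss and correlation 0.7; about 0.1 at 80% retention with correlation 0.6 (0.30 becoming 0.20 or 0.41); nothing under random loss; about 0.01 when the mechanism is shared. The correlations, the true effect and the loss mechanism are all assumed, so these figures show a range and not a forecast. Different collection modes make arm-differential loss plausible but do not establish it or its direction.

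This is a worthwhile improvement to an exploratory analysis. It does not threaten the feasibility outcomes.

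**What to change.** State that the 9-month between-arm difference in QLQ-C30 will be estimated from a mixed model for repeated measures. The model should use baseline, 6- and 9-month scores with arm-by-visit terms, in all randomised women with available scores. Including the pre-randomisation baseline matters, because a model of the two later visits alone would drop women lost before 6 months.

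Standardise the difference by the 9-month SD. Report the SD at each visit and the correlations between visits, all with confidence intervals; a full trial with repeated QoL needs them for sizing. Keep the raw final-score comparison as descriptive. If the SAP already specifies such a model, a sentence bringing the article into line is enough.

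The cost is a few lines of wording and slightly more analysis work, with no new data. With few patients the covariance structure may need simplifying, and a fallback should be named in advance. The precision gain in step 4 assumes complete 6-month scores and will be smaller if those are also missing. Loss driven by deterioration after 6 months is not repaired by this model.
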